### **5.4 Dose Modification**

Since the agents studied are of very low toxicity, no dose modifications are anticipated and none are permitted.

## **6 Agent Formulation and Procurement**

The Urologic Oncology investigational pharmacist will be responsible for overseeing production, storage, oversight, and blinding of gel-capsules containing the study doses of lycopene, fish oil, or placebo. We have researched several academic laboratories that measure serum levels of lycopene and omega-3 fatty acid [1, 5, 7, 9, 16, 27, 41, 64-67], and will negotiate a contract based on availability and cost before the trial is initiated.

## **Lycopene**

### **Chemical name**

Psi-psi-carotene

### **Other names**

none

### **Molecular formula**

C40H56

### **MW**

536.9

### **Preparation**

15 mg gel capsule

### **Storage**

Room temperature

### **Stability**

<5% degradation by HPLC at 3 years

### **Route of administration**

Oral

### **Reported adverse events, potential risks**

No reported adverse events.

### **Potential drug interactions**

None known.

**Procurement**

Lycopene will be supplied by LycoRed Natural Products Industries Ltd.

**Agent ordering**

Through research pharmacy due to placebo control

**Agent accountability**

Inventory maintained by investigational pharmacy

**Fish oil****Chemical name**

Omega-3 unsaturated fatty acid

**Other names**

Docosohexaenoic acid

**Molecular formula**

22:6,n-3

**MW**

356.8

**Preparation**

1g gel capsule

**Storage**

Room temperature

**Stability**

Expiration in 06/2008

**Route of administration**

oral

**Reported adverse events, potential risks**

Allergic reactions to gelatin capsule, fish. Patients may smell like fish.

**Potential drug interactions**

Since omega-3 fatty acids alter prostaglandin levels, patients on long-term treatment with NSAIDS, Cox-2 inhibitors, and/or aspirin may have increased bleeding tendency. Patients on these agents are excluded from the trial.

**Procurement**

Fish Oil will be supplied by Roche Vitamins Inc.

**Agent ordering**

Through research pharmacy due to placebo control

**Agent accountability**

Inventory maintained by investigational pharmacy.

**7 Dose Modifications**

Various doses have been used in previous clinical trials of lycopene and fish oil. Lycopene has been administered in clinical trials at 13.3 mg[30], 15mg[16, 27, 29] [31], 25mg[64], and 30mg per day[28, 68]. No patient enrolled in these trials was reported to suffer an adverse effect while taking lycopene or during follow-up. Omega-3-enriched fish oil also has been administered at a variety of doses in the clinical setting as well - 10g for twelve weeks[41], 6g for eight weeks[69], 6g for up to 28 months[70], 5.2g for six weeks[71], 3.4g for six months[72], 1.65g EPA and DHA for two years[73], and 0.85g for 3.5 years[67]. These trials also demonstrated no adverse effect to patients while taking omega-3 fatty acids in the form of fish oil supplements or during follow-up.

We will proceed with giving 30mg of lycopene or 3g of fish oil doses for the MENS study. These doses have been selected based on the minimal and maximal range at which previous

clinical trials have observed physiologic effects and no toxicity for lycopene and fish oil supplementation. We selected an intervention duration of three months based on previous studies by other groups which documented gene expression changes[15, 16, 41]

## **8 Study Assessments**

### **8.1 Registration**

CRA will assess eligibility, and perform block randomization if appropriate. The investigational pharmacist will provide the patient with blinded capsules and a standard multivitamin. Follow up visits will be arranged, and coordinated with the urologist to ensure tissue acquisition at biopsy visits.

### **8.2 Screening assessments**

#### **Baseline assessment—Clinical**

Before beginning the study a medical history and physical examination, including a digital rectal exam, will be done. On entry into the study, patients will undergo a limited core biopsy by [name] or another urologist from the UCSF Urologic Oncology Department to procure fresh tissue for genomic analysis. Patients who have already donated core biopsies at the time of diagnosis for the Prostate Cancer Tissue Bank will be asked to participate if they meet the inclusion criteria, but will not need to be re-biopsied. Standard clinical history and physical exam, including digital rectal exam, will be performed, and serum will be assayed for PSA, free PSA, testosterone, estrogen, lycopene, omega-3 fatty acid, omega-6 fatty acid, IGFBP-3, and IGF-1. Tissue biopsies for research purposes will also be sent for standard pathologic examination. All patients will fill out a survey instrument characterizing their dietary habits, the Willett SFFQ, a validated food questionnaire as well as a food diary to be completed daily for 3 days prior to the biopsy. All patients will also complete a Health and Prostate Cancer Survey at baseline and at 3 months.

In addition to any prostate biopsy obtained above, serum and urine will be obtained and frozen for future analysis. These samples will be used to investigate the presence of any proteins identified in the gene discovery process. There is currently a CHR protocol in place (99394 CHR#H7720-10671-05) for the collection of cancer specimens for the study of molecular changes.

## **Baseline assessment—Molecular**

**Tissue** - If a patient consents, core needle biopsy tissue will be collected in a standard fashion via transrectal ultrasound guided biopsy. Some tissue will be used immediately for testing. Any remaining tissue will be stored at the UCSF Comprehensive Cancer Center Tissue Bank for possible future research. Samples will only be obtained from patients who give written informed consent. Samples become property of the UCSF Tissue Bank and may not be transferred to another institution. Other investigators will have access to this tissue only with patient consent and through approval of the UCSF Tissue Bank Committee. Tissue samples will receive a unique identifier to protect confidentiality and link clinical outcome to patient samples. Patients may withdraw consent at any time and any unused samples will be destroyed.

**Blood** - Approximately 36ml of peripheral blood will be collected. Samples will be assigned a unique identifier to protect confidentiality and facilitate data analysis.

**Urine** - Approximately 20ml of urine will be collected. Samples will be assigned a unique identifier to protect confidentiality and facilitate data analysis. Urine will be given to the Cancer Center Tissue Core Laboratory, and frozen for future study.

An aliquot of total RNA from dissected normal prostate tissue from each core needle biopsy will be directly reverse transcribed and assessed using Taqman quantitative PCR for *IGF-1* and *PTGS2/COX2*[74-76].

cDNA array hybridization: Patient Test and reference pool fluorescent RNA will be mixed with 20 micrograms of Cot-1 DNA and purified away from unincorporated dye using a Qiagen PCR purification spin column. The column eluate will be dried by lyophilization, and dissolved in a hybridization mixture with a final concentration of 3XSSC, 0.3%SDS, 0.05M Hepes pH7.0, and 10mg/ml polyadenylic acid. The hybridization solution will be denatured by incubation at

94C for 4 minutes to denature the DNA, and applied to the slide under a 25x40 mm cover slip (lifter slips, Eerie Scientific). Hybridization reactions will be allowed to proceed at 63.5C for 14-16 hours with slides contained in a Plexiglas chamber (HybeChamber, Genemachines, Redwood City, CA) submerged in a water bath. After hybridization, each slide will be washed in 2X SSC, 0.2% SDS for 5 minutes at 65C in a Coplin jar, followed by 4 minutes in 2X SSC at room temperature on a gently agitating rotator platform, and 1 minute in 0.065X SSC at room temperature. Excess liquid will be removed from slides by spinning at 600 rpm in a Beckman Allegra clinical centrifuge.

Arrays will be imaged with a confocal laser scanning microscope (Axon 4000B). Post image-acquisition data analysis will be performed with Genepix 3.0 software (Axon), and ratio information corrected for background fluorescence will be uploaded into a relational database (NOMAD, Derisi lab, UCSF unpublished) housed on the laboratory Linux web server. NOMAD will then be queried to produce normalized datasets that can be manipulated by other analysis algorithms. There is no consensus on how to normalize array data across groups working in gene expression profiling. Our approach, implemented by NOMAD software is to make the sum of signals in each channel, cy3 and cy5, equal. Though it may be that more up- or down-regulation is present in the cy3 or cy5 channels for a particular nutritional intervention, we assume that averaging across the large number of genes present on each array will allow identification of modulated genes. The identification of *caspase-3* regulation in prostate cancer attests to the practicality of this approach (unpublished data, [name] lab).

Initial microarray studies will collate sets of named and novel genes that are differentially expressed according to baseline dietary intake quartiles using supervised and unsupervised hierarchical cluster analysis[62] and statistical analysis for microarrays (SAM)[63], a software package that implements a permutation T-test to identify genes up- or down-regulated with a measure of statistical confidence.

We will select particular genes whose expression is correlated with baseline dietary intake for validation of activity of the supplement by an independent assay technique. Quantitative PCR accomplished with the Taqman technology[74-76] is ideally suited to target validation for the MENS study, since the RNA amounts available from clinical core needle biopsies range from 100-600 nanograms. These small amounts of RNA preclude the use of other techniques such as

Northern blot analysis, and are more easily modified for high throughput analysis of several gene targets as compared to RNase protection – RNase protection experiments are also cumbersome due to requirements for radioisotope use. The UCSF Comprehensive Cancer Center has a genomics core available to [name] laboratory which will carry out Taqman quantitative PCR[74-76]

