For the secondary specific aims (aims 1.2 through 1.4 defined above), we will consider a microarray dataset with measurements for 30,000 genes. For this exploratory investigation genes will be treated as being independent so as to first identify all possible genes that may indicate an effect due to the nutritional supplement (Aim 1.2) or to other dietary components (each considered as a binomial variable) (Aim 1.3). Fisher's exact test will be used to determine which genes result in differences in proportions with up or down regulated genes between groups. No adjustment for multiple comparisons will be made. Also, after all patients have had the potential to be followed for at least one year, they will be classified as to whether they had experienced disease progression within 1 year from protocol entry. The same exploratory techniques described above first using the baseline gene expression profile will be carried out to identify genes that may be associated with disease progression (Aim 1.4). Even though any nutritional supplement will be stopped at 3 months from the start of protocol therapy and the duration of any effect is unknown, this analysis will be repeated using the 3-month gene expression profile to identify the effects of any gene that might have been modified by protocol treatment. To account for genes with highly variable expression regardless of study arm, genes whose expression levels change two-fold in more than 20% of men on placebo (comparing three-month to baseline) will

be excluded from subsequent consideration. This might exclude possible predictors of outcome, but if there is variability within the placebo group then the results may be biased. This refining process will isolate potential predictors of nutritional change when assessing the primary as well as the secondary outcomes. Standard microarray gene expression software algorithms will facilitate analyses to determine if there are individual genes or clusters of genes associated with either supplement, dietary component or disease progression[62, 63] . Fisher's exact test will be used to determine which genes result in statistically significant differences between the groups.

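### Equalising total cy3 and cy5 signal weights genes by brightness, so a supplement effect on bright genes can shift all other genes on that arm's three-month arrays

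*Protocol*

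**What the plan says.** Section 8.2 (Baseline assessment—Molecular) describes two-channel arrays: "Patient Test and reference pool fluorescent RNA will be mixed" on each slide. It states that the field has no agreed normalisation, and that the laboratory's software will "make the sum of signals in each channel, cy3 and cy5, equal". It then names the weak point: "Though it may be that more up- or down-regulation is present in the cy3 or cy5 channels for a particular nutritional intervention". Its answer is that "we assume that averaging across the large number of genes present on each array will allow identification of modulated genes", supported by unpublished in-house work on one gene in prostate cancer. Section 8.3 applies the same processing to the follow-up tissue.

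Section 13 sets out how the arrays are used for the secondary aims. On the dataset: "we will consider a microarray dataset with measurements for 30,000 genes". On the test: "Fisher's exact test will be used to determine which genes result in differences in proportions with up or down regulated genes between groups". On multiplicity: "No adjustment for multiple comparisons will be made". A filter drops "genes whose expression levels change two-fold in more than 20% of men on placebo". Section 3.2.2.1 adds clustering and a permutation t-test, with confirmatory Taqman PCR only if enough nucleic acid is left.

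**The concern.** The averaging argument would hold if each of the 30,000 genes had equal weight in the scaling factor. In a sum of intensities the weight is the signal itself, so a modest set of abundant transcripts can carry much of the factor. If a supplement lowers those transcripts, the patient channel is scaled up to match the reference pool and unaffected genes on that man's three-month array look raised. If it raises them, unaffected genes look lowered.

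The planned safeguards do not address this:

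- Randomisation and the placebo comparison do not cancel the offset, because the treatment effect causes it.
- The variability filter looks only at men on placebo, who do not carry it.
- A permutation t-test reads a systematic offset between arms as a real difference.

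At stake is mainly Aim 1.2, the search for new candidate targets. An offset in one arm would add false candidates in one direction and hide true ones in the other. Follow-up PCR can weed out false candidates but cannot recover genes that were never listed.

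**Working it through.** The protocol gives no figure for the normalisation, so there is none to reproduce.

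**Inputs from the protocol.** 30,000 genes; 29 men per arm; two-fold calls; Fisher's exact test per gene; exclusion of genes changing two-fold in more than 20% of placebo men.

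**Assumptions, not in the protocol.** Log-normal intensities with SD of ln signal σ = 1.0, 1.5 or 2.0. The brightest 1% (300 genes) all halve in every man of one supplement arm. Log2 changes within men are normal, with 10% of placebo men two-fold in each direction. Two-sided level 0.05, as section 13 sets no level for the array tests.

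**Step 1: the offset.** If genes with share s of the patient channel change by fold f, the channel total becomes 1+s(f-1) times its old value. Equalising sums multiplies every unaffected gene by 1/(1+s(f-1)).

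- s = 1%, halved: 1/0.995 = 1.005, or +0.007 log2.
- s = 10%, doubled: 1/1.10 = 0.909, or -0.14 log2.
- s = 20%, doubled: 1/1.20 = 0.833, or -0.26 log2.
- A false two-fold shift needs s(f-1) = 1, for example half of all signal tripling.

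**Step 2: share held by the brightest 1%.** Share = Φ(σ - 2.326); offset when halved = -log2(1 - share/2).

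| σ | Share | Offset (log2) |
|---|---|---|
| 1.0 | 0.092 | +0.07 |
| 1.5 | 0.204 | +0.16 |
| 2.0 | 0.372 | +0.30 |

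**Step 3: effect on a null gene.** Ten per cent beyond one log2 unit gives SD = 1/1.2816 = 0.78. The standard error of the arm difference is 0.78 × √(2/29) = 0.205. The chance of an up-call in the supplement arm is Φ((-1 + offset)/0.78), against 0.10 on placebo. Fisher rates below are exact binomial sums for 29 against 29. The t rates use the noncentral t with 56 degrees of freedom and noncentrality offset/0.205.

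| Offset | Up-call rate, supplement | Fisher rejection, up-calls | Per 30,000 genes | t-type rejection |
|---|---|---|---|---|
| 0 | 0.100 | 0.9% | about 260 | 5% |
| 0.07 | 0.116 | 1.1% | about 340 | 6% |
| 0.16 | 0.140 | 2.1% | about 640 | 12% |
| 0.30 | 0.184 | 6.4% | about 1,920 | 30% |

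For down-calls the Fisher rate stays at 0.9%, then 1.1% and 1.8% at the two larger offsets.

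**Step 4: the placebo filter.** More than 20% of 29 (5.8) means six or more men. If changes in either direction count, the total follows Bin(29, 0.20) and P(6 or more) = 0.54, so about half of genes this variable are dropped. If one direction counts, Bin(29, 0.10) gives 0.06. Falsely up-called genes tend to have few placebo up-calls and so survive more often. Given a placebo up-calls, the down-calls follow Bin(29 - a, 0.1/0.9), and the gene stays if the total is at most five. The counts then become about 110, 220, 490 and 1,480 in place of 260, 340, 640 and 1,920.

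**Step 5: a robust alternative.** In simulation with the brightest 300 of 30,000 genes halved (σ = 1.5 and 2.0), centring on the median log ratio leaves an offset below 0.01 log2.

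**The case against.** The strongest reply is that this is a disclosed choice in an exploratory analysis. The protocol says that no consensus exists, names the imbalance and states its assumption. It contains no arithmetic error or contradiction. Nothing in it shows that a few genes dominate the signal, or that either supplement alters the brightest ones. Halving all 300 brightest genes in every man of an arm is a severe scenario; if 300 typical genes (1% of signal) halved, the offset would be 0.007 log2. The arrays seek candidates for further study, with no multiplicity adjustment by design, and PCR confirmation does not depend on array scaling. The median and intensity-dependent methods also assume that most genes do not change.

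Most of this stands, and it limits the size and reach of the point. It does not rescue the averaging argument, which is wrong about what a sum does. Disclosing the risk does not control it, and PCR confirmation depends on leftover sample.

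A reader might infer three stronger things that the document does not support:

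- **That a false difference on all 30,000 genes is certain.** It depends on s and f, which the protocol does not give.
- **That null genes are flagged at 12% to 30% in place of 5%.** Those are t-type rates in the two more severe scenarios. They bear on the permutation t-test family, whereas the Fisher test of section 13 is much more conservative.
- **That the primary result is affected.** It rests on Taqman PCR normalised to a housekeeping gene, not on array totals.

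**Conclusion.** The concern holds in conditional form. The sum rule is sensitive to regulation of bright genes, the protocol's stated defence does not cover this, and no planned step removes it. The distortion is negligible when the changing genes hold about 1% of signal and becomes material from roughly 10% to 20% upward. In the brightest-300 scenario, false up-calls by Fisher's test rise by a factor between about 1.3 and 7 before the filter (1.1/0.9 from unrounded rates, up to 6.4/0.9). That range rests on assumed intensities, a uniform halving and an assumed within-man variability. Exposure is limited to the exploratory array aims (1.2 to 1.4, mainly 1.2). This is a cheap improvement worth making, not a threat to the trial's main conclusion.

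**What to change.** In section 8.2, replace equalising of channel sums with centring each array on the median (or a trimmed mean) of the background-corrected log ratios, or with an intensity-dependent fit such as lowess. Apply the same rule to all baseline and three-month arrays, and keep the sum-normalised result as a sensitivity analysis.

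The cost is a software setting and a sentence or two of protocol text. Stored scans can be re-normalised, so no new biopsy or laboratory work is needed. There are two downsides: values will not match the laboratory's earlier sum-normalised data unless those are reprocessed, and the replacement still assumes that most genes are unchanged.

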## 1. Objectives

- 1.1 Primary: To measure gene expression in normal prostate tissue acquired by needle biopsy in men assigned to placebo, lycopene or fish oil nutritional supplements at baseline and after intervention. The primary outcome measure is a two-fold decrease in mRNA transcript level. The primary study endpoint is the difference in the proportion of the patients in a nutritional supplement arm compared to a placebo control arm achieving a two-fold decrease in the gene of interest. Quantitative polymerase chain reaction will assess modulation of expression of the *insulin-like growth factor 1 (IGF1)* and the cyclooxygenase 2 (*Cox-2*) gene in lycopene and fish oil recipients respectively.
- 1.2 Secondary: We will use cDNA microarrays with 30,000 independent clones to identify new candidate molecular targets for lycopene and omega-3 response pathways deserving further study.
- 1.3 Secondary: To correlate baseline gene expression patterns determined by cDNA array analysis with self-reported dietary intake. Based on previous epidemiologic, *in vitro*, and *in vivo* studies, we hypothesize that higher intake of total energy, fat/meat/animal products, dairy/calcium, and lower intakes of fish, vegetables, tomatoes/lycopene, vitamin E, and selenium will be associated with particular gene expression profiles.
- 1.4 Secondary: We will assess if there are gene expression patterns correlated with progression or lack of progression as assessed at a time point 12 months after study entry.
- 1.5 Secondary: We will assess if lycopene or omega-3 supplements affect the incidence of tumor progression.

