##### **3.2.2 Secondary efficacy outcome measures**

- 3.2.2.1 The secondary aim of identifying genes correlated with nutritional supplementation with lycopene or fish oil will be accomplished by analyzing gene expression of 30,000 human genes using a cDNA array. Identification of a gene cluster associated with lycopene or fish oil but not placebo will be

accomplished using hierarchical clustering[62], or alternate algorithms that use permutation t-test statistics to account for the multiplicity of tests accomplished using such large scale microarrays[63]. If sufficient nucleic acid samples remain after primary outcome measure assessment, and microarray analysis, confirmatory Taqman quantitative polymerase chain reactions will be used to confirm the specific induction of genes identified in these studies by lycopene or fish oil.

- 3.2.2.2 To accomplish the secondary aim of identifying genes correlated with baseline dietary intake, patients will be stratified for high and low intake of total energy, fat/meat/animal products, dairy/calcium, fish, vegetables, tomatoes/lycopene, vitamin E, and selenium as defined by the Willett Semi-quantitative Food Questionnaire. Separate microarray data analyses will be performed for each dietary factor by placing all patients with low intake ( $\leq$  median) into the first half of the data table, and subsequently all patients with high intake ( $>$  median). The same standard microarray hierarchical clustering and permutation t-test approaches as in 3.2.2.1 will then be used to identify genes whose expression differs between these groups.
- 3.2.2.3 We acknowledge that the study is underpowered to assess effects of nutrition supplementation on progression rates, given the heterogeneous nature of prostate adenocarcinoma. Nevertheless, it is compelling to perform exploratory data analysis to examine whether exploratory analysis may detect genes correlated with progression or lack of progression at 12 months in the MENS study. If any correlates are detected, they will be used to formulate a hypothesis for testing in further large scale studies, such as the multi-institutional CALBG or SWOG watchful waiting trials.
- 3.2.2.4 With watchful waiting, approximately 25% of patients will experience disease progression when assessed 12 months after study entry. To assess whether the

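### Exploratory Aim 1.3 (baseline diet and gene expression) has three descriptions of the diet variable and two deciding tests; they yield overlapping but not identical gene lists, and grouping costs power

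*Protocol*

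**What the plan says.** Section 1 words Aim 1.3 as a correlation: "To correlate baseline gene expression patterns determined by cDNA array analysis with self-reported dietary intake". Three later places turn it into an analysis.

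- **Section 3.2.2.2:** "patients will be stratified for high and low intake of total energy" and seven further dietary factors. Each factor is handled separately, with low meaning at or below the median and high meaning above it. Then: "The same standard microarray hierarchical clustering and permutation t-test approaches as in 3.2.2.1 will then be used".
- **Section 8.2, Baseline assessment (Molecular):** the initial array work is to collate genes "differentially expressed according to baseline dietary intake quartiles using supervised and unsupervised hierarchical cluster analysis", together with SAM, which the protocol describes as a permutation t-test. Genes selected for their relation to baseline intake then go to Taqman confirmation, from biopsies yielding 100 to 600 ng of RNA.
- **Section 13:** the screen looks for genes that may respond to the supplement "or to other dietary components (each considered as a binomial variable) (Aim 1.3"), and "Fisher's exact test will be used to determine which genes result in differences in proportions with up or down regulated genes between groups". There are 30,000 genes and no multiplicity adjustment. Standard array software is said to support the analysis, and Fisher's exact test is then named again as the test of significance.

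**The concern.** The product of Aim 1.3 is a list of genes per dietary factor. Which genes are on it depends on how intake is coded and on which test decides. The protocol fixes both, but not in the same way in each place, so this is not a detail merely left for a later analysis plan. With eight dietary factors, 30,000 genes and no adjustment, an open choice of rule can be settled after the results are seen, and the list chosen determines which genes use scarce RNA for confirmation.

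There is also a question of efficiency. The food questionnaire gives graded intake and the aim is worded as a correlation, yet none of the three sections tests intake in graded form.

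**Working it through.** **1. The sections side by side**

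| Section | Intake coded as | Deciding test |
|---|---|---|
| 3.2.2.2 | two groups, cut at the median | clustering, permutation t-test |
| 8.2 | quartiles | clustering, SAM (permutation t-test) |
| 13 | binary, cut not named | Fisher's exact test on proportions up- or down-regulated |

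Sections 3.2.2.2 and 8.2 use the same baseline arrays, baseline diet and software references, so they are not two separate analyses. Section 8.2 does not say how quartiles enter a t-test: top against bottom, trend, or four groups. The medians in section 13 (4 servings of tomato and two of fish per week) are pilot values for the randomisation strata, not a stated cut for this aim.

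**2. Number of men.** The protocol gives no power figure for Aim 1.3, so there is none to reproduce. Its accrual figure does reproduce: 87 / 0.90 = 96.7, rounded up to 97. The 10% loss occurs by the three-month biopsy, so a baseline analysis can use about 97 men.

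**3. Efficiency of grouping** (assumed: intake normal, expression linear in intake). A median-split indicator has squared correlation 2/π = 0.637 with intake, so 97 × 0.637 ≈ 62 men's worth of information. The corresponding values are 0.81 for top against bottom quartile and 0.86 for a trend score across quartiles.

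**4. Simulation, 97 men, two-sided tests.** Assumed: bivariate normal intake and log expression. The correlations r and the thresholds are also assumptions, because the protocol states none for this aim. Overlap is the number of genes called by both rules divided by the number called by either, for median split against top-versus-bottom quartile.

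| r | p below | Median split | Four quartile groups | Top v bottom quartile | Rank test | Overlap |
|---|---|---|---|---|---|---|
| 0.3 | 0.001 | 17% | 16% | 23% | 33% | 36% |
| 0.4 | 0.001 | 46% | 48% | 59% | 73% | 58% |
| 0.3 | 0.05 | 66% | 63% | 75% | 81% | 72% |

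At r = 0.5 and p<0.001 the overlap is 83%.

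**5. Null genes.** At p<0.05 the two rules share about 18% of the null genes called with 87 men, and about 20% with 97. If all 30,000 genes were null, each rule would call about 30,000 × 0.05 = 1,500 per dietary factor. With a shared count s, s / (3,000 − s) = 0.18 to 0.20 gives s ≈ 460 to 500. Roughly 1,000 false calls on each list would therefore be absent from the other.

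**6. The test named in section 13.** As an illustration, with expression cut at its own median (an assumption), Fisher's test on a median split of intake has about 44% power at r = 0.3 and p<0.05 with 97 men. The t-test on the same split has 66%. The choice of test therefore matters as well as the coding of intake.

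**The case against.** The outcome section and the statistical section agree on two groups, and 3.2.2.2 gives an exact cut. Quartiles appear once, in laboratory methods text describing initial array work, and they nest within a median split. A sensible reader would let 3.2.2.2 and 13 govern. That is fair and lowers the weight of the point. However, the protocol never says so, and the two-group reading does not settle the conflict between the permutation t-test and Fisher's exact test. Section 13 does cite the array software as well, but it gives the significance decision to Fisher's test.

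A reader might infer from the 36% figure that the rules pick largely different genes. The calculations do not support that in general: overlap rises to 58% and 83% with stronger correlation, and is 72% at r = 0.3 with the looser threshold. Part of the low figure simply reflects low power at p<0.001; there, the median split overlaps even the rank test by only about 43%.

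A reader might also infer that the trial's main conclusion is exposed. It is not: the aim is labelled exploratory, is meant to cast a wide net, and is followed by confirmation with an independent assay.

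Finally, preferring graded to grouped intake is a judgement about efficiency, not an error in the text. The gain depends on a roughly monotone relation. A true step at the median would lose nothing under the split, though the protocol gives no reason to expect one.

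**Conclusion.** The inconsistency stands. For one aim, intake is a median split, an unspecified binary variable and quartiles, and the deciding test is a permutation t-test in two places and Fisher's exact test in the third. The consequence is moderate: overlapping but not identical lists of true associations, and poor agreement on false ones.

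Separately, and only under a roughly monotone relation, grouping loses useful power: at r = 0.3 a rank test roughly doubles the median split's power at p<0.001 and adds 15 points (81 − 66) at p<0.05. The wording conflict is certain. The sizes rest on assumed normality, correlations and thresholds. The primary endpoint and sample size are untouched, so severity is low.

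**What to change.** State one rule for Aim 1.3 in 3.2.2.2, 8.2 and 13: test each gene against each dietary factor as ranked continuous intake over all men with baseline arrays, with permutation p-values (for example SAM with a quantitative response).

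- **3.2.2.2:** name this test and keep the median split for display only.
- **8.2:** remove the reference to quartiles.
- **13:** remove the binomial coding of dietary components **and** replace Fisher's exact test for this aim. Removing the coding alone would leave a test of group proportions that cannot take ranked intake. Fisher's test for the other aims need not change.

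If the sponsor prefers groups, one grouping and one test must still be stated in all three places.

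The cost is text edits and similar analysis effort, with no extra patients, tissue or assays. The drawback is less sensitivity to non-monotone associations.
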